**Figure 2 figure2:**
[figure not shown]
Schematic of asynchronous video directly observed therapy (VDOT) system.

**Figure 3 figure3:**
[figure not shown]
Video directly observed therapy (VDOT) SMS text messaging system.

#### Follow-up of Participants With Missed Videos or Study Visits

A predefined follow-up protocol will be used to contact study participants in cases of missed doses or videos. The research staff will make 2 phone call attempts within the first 24 hours of a missed, expected video to establish dosing history and the reason for missing videos. If there is no response from the participants within 72 hours, the research team will escalate the follow-up to a field visit to trace the participant at home or work. After a period of 2 weeks from when the intensive, active follow-up protocol has been completed, there will be a waiting interval of 2 weeks, hoping that the participant will call back or return to the clinic for a routine visit. If the participant does not show up for the scheduled clinic visit, the national TB program staff will get involved in support of the patient. A declaration of “lost to follow” will be made if the participant does not return for 2 consecutive months, in line with the standard World Health Organization’s guidelines [34].

#### Criteria for Discontinuing or Modifying Allocated Interventions for Trial Participants

Patients may voluntarily withdraw from the study for any reason, at any time. After consultation with the protocol chair, the investigator may also withdraw participants from the study to protect their safety or if patients are unwilling or unable to comply with the required study procedures. Reasons for all cases of nonadherence and nonretention will be retrieved and documented in case report forms. Randomized patients who are prematurely discontinued from the study at any time will have their clinical and laboratory evaluations performed, if possible, and will also continue receiving treatment for TB and routine health services. According to standard definitions provided by Friedman et al [35], a participant who is assigned to the VDOT but who fails to adhere to the intervention will be considered a dropout, whereas a participant who discontinues the intervention but continues to take treatment under the usual-care procedures will be considered a cross-over [35]. Participants who withdraw, dropout, or cross-over will be included in the primary intention-to-treat analysis.

### Study Outcomes

The primary outcome measure is the level of adherence calculated as the fraction (proportion) of expected doses observed (FEDO) over the 6 months of treatment or by the end of the study following randomization. Since direct observation as a way of measuring medication adherence may be challenging to employ consistently in the UC-DOT group, we will also use self-reports and pill counts as indirect measures of adherence and then triangulate the results. Time-to-treatment completion will be assessed as the main secondary outcome. Other outcomes will be sputum smear conversion at 2 and 6 months or the end of treatment, clinical response as a measure of self-reported improvement in TB symptoms, and weight gain at 2, 4, and 6 months or the end of treatment. Other outcomes will be self-reported side effects, the occurrence of adverse events, and patient satisfaction at the exit of the study. Patient satisfaction will be evaluated in 2 ways: (1) overall satisfaction with VDOT or UC-DOT, and (2) satisfaction with specific areas, such as the VDOT technology and app use; information and training received; interaction with treatment supporters, health providers, or research staff; and privacy and confidentiality during medication intake. Additionally, at study exit, we will conduct individual qualitative interviews for both UC-DOT and VDOT participants to capture detailed information about participant experiences during the study.

Study measurements will be done at baseline and follow-up at months 2, 4, and 6 to ensure close monitoring of all patients in treatment. All participants, regardless of the study group, will complete a questionnaire at these follow-up visits (Multimedia Appendix 2 and 3). The follow-up questionnaire will address issues such as (1) patients’ current use and any changes in experience with a cell phone, such as acquiring a personal cell phone or smartphone; (2) transportation and other costs to and from the TB clinic; (3) TB treatment experiences using VDOT or UC-DOT; (4) experiences when using a phone to record videos or when receiving support under the usual DOT; (5) satisfaction with TB and VDOT or UC-DOT; (6) ongoing support received during treatment; (7) side effects experienced; (8) difficulties with medication supply or transportation to the clinic; and (9) privacy, confidentiality, and stigma concerns. For internal validity, adherence will also be measured at follow-up visits by pill counts (when possible) and using a 10-item self-reported adherence questionnaire [36] (Multimedia Appendix 4).

### Qualitative Exit Interview

In-depth interviews will be conducted at the exit of the study to gather detailed information to enrich the understanding of the quantitative data. This will involve intensive individual interviews with a small number of study participants to explore their general experiences, operations, processes, and outcomes that they perceive as resulting from their involvement in VDOT or usual-care DOT. We will also specifically probe the participants’ experiences of stigma, privacy, gender, and socio-cultural issues. To ensure representation of a wide variety of views, participants will be purposively selected based on sex, age, and observed experiences during the time in the study. For example, we will ensure both younger and older and male and female participants are included. In terms of treatment experiences, patients with low, moderate, and high adherence will also be selected accordingly. We will aim to interview a total of 20-30 patients with equal numbers from each study arm. The final number of participants to be interviewed will be determined based on the attainment of thematic saturation (ie, the point at which interviewing more respondents will yield no new information on the topics of interest) [37]. Interviews will be audio-recorded and transcribed. We will use thematic analysis to code, identify key patterns or themes, and then summarize the findings. ATLAS.ti software (version 9; ATLAS.ti Scientific Software Development GmbH) will be used in the coding and detailed processing of the data.

### Data Management

All study questionnaires will be administered using electronic forms on ODK (Open Data Kit) using laptops or tablet devices. Data in the form of videos collected from the VDOT system will be held on a secure HIPAA-compliant cloud server and will be backed up nightly locally in Uganda. Weekly data integrity reports will be run on the system using an automated routine. Monthly data exports will be made, and data will be merged into the master data file. The master data file will be stored at the University of Georgia on a password-protected network with access restricted to study personnel. This will be automatically backed up daily. The master data file will use the unique study number allocated at the time of randomization but will not include personal identifier information. This identifiable information will be held in a separate password-protected file on the same network drive in the form of a lookup table.

### Sample Size

This trial is powered on the primary outcome measure and based on a comparison of the medication adherence level between the UC-DOT group and the VDOT group. The calculated sample size is 124 in order to achieve a chi-square test difference of 0.85 versus 0.63 (difference 0.22 and odds ratio 0.30) between the groups. We assumed an attrition rate of 14%, guided by published literature; this was based on a randomized controlled trial comparing a digital adherence intervention and usual care in Kenya in which the overall loss to follow-up rate was 11.7% (9.9% in the usual-care DOT arm and 1.76% in the digital intervention arm) [38]. By inflating the attrition rate to 14%, we erred on the higher side of attrition. In contrast, another RCT of asynchronous VDOT done in the United Kingdom had a higher attrition rate of 23%; however, the study population was very different from our current study in that it included 58% of homeless subjects [15]. At a 14% attrition rate, the estimated final sample size was 144 participants with 72 subjects per group. This would provide a power of 80% to detect a 22% difference in the primary outcome between the 2 comparison groups (85% VDOT vs 63% DOT) based on a 2-sided significance level of 5%. Sample size tables were used to estimate precision. All calculations were performed using the SAS statistical software package (version 9.3; SAS Institute).

### Statistical Analyses

Intention-to-treat analysis will be conducted where all patients will be analyzed according to the arm to which they were originally randomized. VDOT treatment observations will be classified as completed if ingestion of all medicines is observed, or if videos are received but not viewable because of a technical complication (given that patients would have no control over whether videos were corrupted). The sensitivity analysis will consider only videos for which all medications are observed as completed. An adherence proportion will be observed for each individual in this study. Let p_ij_ be the adherence proportion for individual j (j=1, ..., n) in treatment group i (i=0 for VDOT and i=1 for UC-DOT). Then, let p_0_ and p_1_ equal to the average FEDO in the VDOT and UC-DOT arms, respectively. Similarly, let s_0_=s.e.( p_0_) be the standard error of p_0,_ and similarly, let s_1_ be the standard error of p_1_. The standard *t* test statistic will be used to calculate a *P* value based on the following statistic:

The Welch *t* test will be used to calculate significance. However, since we do not have estimates of s_0_ and s_1_, this formula is not useful for power calculation. Therefore, to calculate power and sample size, we treat the response for each individual as binary (0 or 1), indicating adherence or nonadherence. This corresponds to using an adherence cutoff value of FEDO with equal-to or greater than 80% as a threshold for adherence. This binary response variable for adherence will be used in the final analysis to facilitate comparison with previous clinical trials [15].

Univariate statistics will be used to describe the baseline characteristics of the study population, the prevalence of individual clinical responses, and the level of adherence. Similar analyses will be repeated for secondary outcomes. Multivariable logistic regression analyses will be done to test for significant associations between study groups (VDOT/ UC-DOT) as the main exposure and the primary binary outcome of adherence (≥80%; yes/no). Age and HIV status are set a priori as potential confounders that will be adjusted for in all the models. Sex will not be adjusted since the randomization is stratified by sex. Other covariates that will be adjusted for in the models include education level, income, and smartphone ownership, previous TB treatment, HIV status, and other clinical variables at baseline. Crude and adjusted odds ratios with 95% confidence intervals will be presented, and statistically significant *P* values will be less than .05.

Secondary analyses of time-to-treatment completion will provide another outcome that can be used to compare the 2 groups according to TB program performance indicators. Survival analysis to compare the median time-to-treatment completion between study groups with associated log-rank tests will be performed. Crude and adjusted Cox proportional hazards regression analyses will be performed to determine factors associated with time-to-treatment completion. Cox proportional hazards ratios with corresponding 95% confidence intervals will be presented. Other analyses comparing trends at months 2, 4, and 6 in adherence, sputum conversion, and clinical response will be performed. These repeated measures data will be modeled as a discrete-time Markov chain or Poisson process [30]. Analyses will be done using Stata (version 14; StataCorp) and R (version 3.3.2; R Core Team) software.

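### The primary comparison of mean FEDO is an unadjusted Welch t test that leaves out sex, age and HIV status; it is valid, but gives up a modest amount of precision at almost no saving

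*Protocol article*

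**What the plan says.** Study Outcomes in the protocol article declares FEDO over the treatment period as the primary outcome. Statistical Analyses defines the two quantities to be compared as "equal to the average FEDO in the VDOT and UC-DOT arms, respectively" and then states: "The Welch *t* test will be used to calculate significance". No covariate enters this comparison. The same section concedes that "since we do not have estimates of s_0_ and s_1_, this formula is not useful for power calculation", and so sizes the trial on the binary version, FEDO of at least 80%.

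The covariates appear one paragraph later, with the multivariable logistic regression of that binary version: "Age and HIV status are set a priori as potential confounders that will be adjusted for in all the models". A longer list follows: "Other covariates that will be adjusted for in the models include education level, income, and smartphone ownership, previous TB treatment, HIV status", together with other baseline clinical variables. On the stratification factor the section says: "Sex will not be adjusted since the randomization is stratified by sex". Under Randomization, however, the article justifies stratifying by sex on the ground that sex matters for adherence to TB treatment.

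**The concern.** Naming age and HIV status in advance for an adherence model presupposes that they are related to adherence. In a randomized trial the main value of such variables is that they remove outcome variance, and a linear model for mean FEDO does that directly. The plan uses them for the dichotomised outcome and leaves the declared primary measure without them.

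The treatment of sex points the same way. Stratification balances sex between arms, so the true sampling variance of the difference no longer contains a contribution from sex imbalance. The Welch standard error is still computed from the total within-arm spread, including differences between men and women. If sex is prognostic, that standard error is too large. Stratification is therefore a reason to include sex, not to leave it out.

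At stake are the width of the primary confidence interval and the power of a test whose power was never established.

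**Working it through.** **1. The plan's own figure.** Inputs from Sample Size: 0.85 against 0.63, two-sided 5%, 80% power, 14% attrition. With mean proportion 0.74 and a pooled-variance chi-square without continuity correction:

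n per arm = [1.960 × √(2 × 0.74 × 0.26) + 0.842 × √(0.85 × 0.15 + 0.63 × 0.37)]² / 0.22² = 61.2, rounded up to 62.

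The total is 124, as stated; power at 62 per arm is 80.5%. Then 124 / 0.86 = 144.2, in line with the stated 144. This 80% belongs to the binary outcome. It says nothing about the Welch test, for which the document gives no standard deviation.

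**2. What adjustment does.** Let R² be the share of within-arm FEDO variance explained jointly by sex, age and HIV status. The document gives no value, so a range is assumed. Residual variance is (1 − R²) times the unadjusted variance, interval width scales by √(1 − R²), and the equivalent sample size is 124 / (1 − R²). For power, suppose the unadjusted test has 80%: power = Φ(2.802 / √(1 − R²) − 1.960).

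| Assumed R² | Interval width | Equivalent evaluable N | Power from an 80% start |
|---|---|---|---|
| 0.02 | × 0.990 | 127 | 80.8% |
| 0.05 | × 0.975 | 131 | 82.0% |
| 0.10 | × 0.949 | 138 | 84.0% |

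A noncentral t calculation (62 per arm, effect 0.507 SD) gives the same power figures to the first decimal. It needs R² of about 0.126 for a gain of 5 points.

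**3. The cost of fitting three covariates.** Residual degrees of freedom fall from 122 to 119. Scaling the variance by 122/119 = 1.025 approximates the price, so break-even is R² = 1 − 119/122 = 0.025. Net variance ratios are:

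- R² = 0.02: 0.98 × 1.025 = 1.005, no gain
- R² = 0.05: 0.95 × 1.025 = 0.974, interval about 1.3% narrower
- R² = 0.10: 0.90 × 1.025 = 0.923, interval about 3.9% narrower

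**4. Dependence on the starting power.** Suppose instead that the planned 85% and 63% above the cutoff came from normal FEDO with equal variances. The difference would be 1.036 − 0.332 = 0.705 SD, and unadjusted power at 62 per arm already 97.3%. Adjustment would raise it to 97.9% at R² = 0.05 and 98.4% at R² = 0.10, gains of about 0.6 and 1.1 points. FEDO is bounded and probably skewed, so this is an illustration too.

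**The case against.** The strongest reply is that nothing here is an error. A Welch test of two randomized arms is valid and unbiased, an unadjusted primary comparison with adjusted supporting models is a common design, and an adjusted analysis of mean FEDO could still appear in an analysis plan that is not shown. The validity point stands in full. The last point does not dispose of the matter, because the article names the test, its inputs, the covariates and the model they enter. The comment is on a stated choice, not on missing detail.

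The size of the gain is also rightly disputed. Both the 80% starting power and every value of R² are assumptions, and age and HIV status may explain little. A reader might carry over the familiar correlation of 0.5 (R² = 0.25), which would lift 80% to about 90%. That convention suits a baseline measurement of the outcome. Participants here are starting treatment or within a month of starting, and no baseline FEDO is described.

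Two stronger readings should also be set aside. A reader might infer that a chance imbalance in age or HIV status would bias the primary result or pass through unexamined. Randomization protects the unadjusted test, and the adjusted odds ratios for FEDO of at least 80% do take account of both variables. A reader might also infer that the plan will treat any gap between crude and adjusted odds ratios as evidence of confounding. Such a gap can arise without confounding, because odds ratios are non-collapsible, but the article says only that both will be presented. Calling the covariates potential confounders is loose wording and no more.

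**Conclusion.** The point holds as a modest loss of efficiency in a stated method. The primary test of mean FEDO carries no covariates, the variables fixed in advance serve only the dichotomised version of treatment-period adherence, and the reason given for omitting sex runs the wrong way. It is not a problem of bias or type I error; if sex is prognostic, the Welch standard error errs on the cautious side.

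The size rests on an R² that the document does not supply. At an assumed 2 to 10%, the interval narrows by about 1 to 5% before the fitting cost, and that cost cancels the gain at the bottom of the range. The matching power gain of about 1 to 4 points holds only if unadjusted power is near 80%; from a higher start it is smaller.

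**What to change.** In Statistical Analyses, make the primary comparison a prespecified linear model of FEDO on arm, sex, age and HIV status with heteroscedasticity-robust (HC3) standard errors, and report the adjusted mean difference with its 95% confidence interval. The HC3 errors keep the allowance for unequal variances that the Welch test provides. Retain the Welch test as the unadjusted supporting analysis. Keep education, income, smartphone ownership and previous TB treatment out of the primary model, so that no choice is left to the analyst.

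In the paragraph on the regression models, delete the statement that sex is not adjusted because randomization is stratified by it, and include sex in the models.

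The change is a few sentences and needs no new data: sex is recorded for stratification, age for eligibility, and HIV status is already a planned covariate. It costs about 3 degrees of freedom, and a rule is needed for missing baseline values. It should be fixed before anyone sees adherence by arm, including at the interim look planned under Data and Safety Monitoring.

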**Methods:**

The DOT Selfie study is an open-label, randomized controlled trial (RCT) with 2 parallel groups, in which 144 adult patients with TB aged 18-65 years will be randomly assigned to receive the usual-care DOT monitoring or VDOT as the intervention. The intervention will consist of a smartphone app, a weekly internet subscription, translated text message reminders, and incentives for those who adhere. The participant will use a smartphone to record and send time-stamped encrypted videos showing their daily medication ingestion. This video component will directly substitute the need for daily face-to-face meetings between the health provider and patients. We hypothesize that the VDOT intervention will be more effective because it allows patients to swallow their pills anywhere, anytime. Moreover, patients will receive mobile-phone–based “social bundle” incentives to motivate adherence to continued daily submission of videos to the health system. The health providers will log into a secured computer system to verify treatment adherence, document missed doses, investigate the reasons for missed doses, and follow prespecified protocol measures to re-establish medication adherence. The primary endpoint is the adherence level as measured by the fraction of expected doses observed over the treatment period. The main secondary outcome will be time-to-treatment completion in both groups.

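### Two different variables are called primary (FEDO as a proportion, and FEDO ≥80% yes/no), and the stated 80% power applies only to the second

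*Protocol article*

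**What the plan says.** Two sections declare the primary outcome as a proportion measured on each patient. The Abstract (Methods) says "The primary endpoint is the adherence level as measured by the fraction of expected doses observed over the treatment period". Study Outcomes says "The primary outcome measure is the level of adherence calculated as the fraction (proportion) of expected doses observed (FEDO) over the 6 months of treatment".

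Statistical Analyses follows this at first. It defines the average FEDO in each arm and a t statistic for the difference, and says "The Welch *t* test will be used to calculate significance". It then explains why power was not worked out for that test: "However, since we do not have estimates of s_0_ and s_1_, this formula is not useful for power calculation". For power and sample size it therefore treats each patient as adherent or not, with FEDO of at least 80% as the cutoff. It adds that "This binary response variable for adherence will be used in the final analysis to facilitate comparison with previous clinical trials".

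Later in the same section, multivariable logistic regression is applied to "the primary binary outcome of adherence (≥80%; yes/no"). Crude and adjusted odds ratios are planned, and P below .05 counts as significant.

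Sample Size says that the trial is powered on the primary outcome measure and describes a chi-square comparison of 0.85 with 0.63. It concludes: "This would provide a power of 80% to detect a 22% difference in the primary outcome between the 2 comparison groups".

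**The concern.** Mean FEDO and the share of patients with FEDO ≥80% are different quantities with different tests, and both carry the label primary. The SAP is not shown and may settle details of method. Which variable is primary is a protocol-level statement, however, and this text gives two answers.

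Three things follow.

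- The two analyses can point in different directions, and no rule settles which one counts. The trial is open-label and adherence by arm is to be checked at the halfway point, so a choice made late would be hard to defend.
- If a significant result on either variable were taken as success, the error rate would exceed the stated 5%.
- A reader who takes the primary outcome from Study Outcomes will read the power statement as 85% versus 63% of doses observed. It actually refers to 85% versus 63% of patients above a cutoff.

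**Working it through.** **1. Reproduce the stated sample size.** Inputs from Sample Size: 0.85 and 0.63, two-sided 5%, 80% power, 14% attrition. Allocation is 1:1 (Randomization). For the pooled chi-square without continuity correction, the mean proportion is 0.74 and

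n per arm = [1.96·√(2·0.74·0.26) + 0.8416·√(0.85·0.15 + 0.63·0.37)]² / 0.22²
= [1.96·0.6203 + 0.8416·0.6005]² / 0.0484
= 1.7212² / 0.0484 = 61.2, rounded up to 62, or 124 in total.

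Power at 62 per arm: Φ[(0.22·√62 − 1.2158) / 0.6005] = Φ(0.860) = 80.5%.

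Attrition: 124 / 0.86 = 144.2, against a stated 144. Odds ratio: (0.63/0.37) / (0.85/0.15) = 0.30, as stated.

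Other versions do not give 124: continuity-corrected 71 per arm, unpooled 58.5, arcsine 59.8, log odds ratio 65.9, one-sided 49. The 80% therefore belongs to the chi-square test on FEDO ≥80%.

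**2. Power for mean FEDO.** The document gives neither an SD nor a difference in means, so every figure here rests on an assumption. With 62 per arm and two-sided 5%, the difference detectable with 80% power is (1.96 + 0.8416)·SD·√(2/62):

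| Assumed SD | Detectable difference in mean FEDO | Power for an assumed difference of 0.10 |
|---|---|---|
| 0.15 | 0.075 | 96% |
| 0.20 | 0.101 | 80% |
| 0.25 | 0.126 | 61% |
| 0.30 | 0.151 | 46% |
| 0.35 | 0.176 | 36% |

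**3. Hold 85% versus 63% at the cutoff and vary only the shape of FEDO.** Simulation, 62 per arm, 20,000 replicates per scenario:

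| Assumed FEDO distribution | Welch power | Chi-square power |
|---|---|---|
| Beta, equal precision in both arms, 2 to 10 | 91–97% | 81% |
| Beta, precision 1 (VDOT) and 5 (UC-DOT) | 76% | about 81–82% |
| Adherent patients uniform on 0.8–1, the rest on 0.6–0.8 | about 65% | 81% |
| The same, with 5 / 10 / 14% in both arms stopping early (FEDO 0–0.3) | 29 / 19 / 16% | about 81% |

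The difference in means is not 22 points in any row. It is about 7–12 points in the equal-precision Beta rows. In the uniform scenarios it is 0.22·(0.9 − 0.7) = 0.044, about 4 points.

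**4. Disagreement between the tests.** Under the equal-precision Beta assumptions with the planned effect, exactly one of the two tests is significant in roughly 12–16% of trials. With early stoppers the gap in power alone forces at least 81 − 29 = 52% to 81 − 16 = 65%.

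**5. Error rate if either test could claim success.** Upper bound: 0.05 + 0.05 = 10%; for independent tests it is 1 − 0.95² = 9.75%. The two tests share the same data, so the actual figure is lower. With Beta FEDO and 63% of patients at or above the cutoff in both arms (62–72 per arm), each test alone is near 5% and at least one is significant in about 7–8%.

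**The case against.** The strongest defence is that the binary variable is a disclosed device. Statistical Analyses says openly that the spread of FEDO was unknown, so power was worked out on a dichotomy. The stated reason for keeping the dichotomy in the final analysis is comparability with other trials, which sounds supportive. The phrase about a primary binary outcome might then mean only the binary form of the primary outcome.

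Part of this stands. The substitution is disclosed, the arithmetic is right, and the article nowhere uses the term co-primary or says that either result is enough. A reader might infer that two tests are each run as primary at 5%. That is an inference from the labels and the single .05 threshold, so the 7–8% is conditional. The two complaints also belong to different readings: if the binary variable is primary, the power statement is correct; if it is not, there is only one primary test. The defect is the ambiguity.

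The defence does not remove the label. Logistic regression is applied to a variable called primary, Sample Size calls the 22-point difference one in the primary outcome, and Study Outcomes defines that outcome as something else.

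A reader might also infer that dichotomising throws away power which the trial already has. The document does not support this. Welch's test does better under equal-precision Beta distributions and worse under the other shapes tried. Early stoppers are realistic, because dropouts stay in the intention-to-treat analysis.

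**Conclusion.** The point holds as an inconsistency in what is primary, together with a power statement attached to the wrong description. The sample size needs no correction for what it actually powers: 62 per arm gives 80.5% for 85% versus 63% of patients with FEDO ≥80%.

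That figure does not carry over to mean FEDO. Power there runs from about 16% to 97% over the assumed distributions, so the document supports neither a claim that mean FEDO is underpowered nor a claim that it is better powered. The error rate of about 7–8% (at most 10%) applies only under an either-test rule that the article does not state, and it depends on the assumed Beta shape. The disagreement figures depend on assumed shapes in the same way.

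**What to change.** Before any analysis by arm, and preferably before the halfway check of adherence, name one primary endpoint with one primary test at two-sided 5%. Label the other secondary or supportive. Align the Abstract, Study Outcomes, Sample Size and Statistical Analyses. Two routes are open.

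- **(a) FEDO ≥80% as primary, with one named test.** The chi-square matches the calculation; crude and adjusted logistic regression are at present also candidates, so one must be chosen. This keeps 124/144 and the stated 80% power. Mean FEDO becomes the key secondary.
- **(b) Mean FEDO by Welch's t test as primary, with the binary variable secondary.** This matches the Abstract and Study Outcomes. State that the 80% power applies to the binary variable, and give power for mean FEDO only under a stated assumed SD and difference.

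Under both routes, reword Sample Size to a 22-percentage-point difference in the proportion of patients with FEDO ≥80%.

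The cost is wording in the protocol, with no extra patients or data. One analysis loses primary status, and under (b) the primary has no firm power figure. Keeping both as primary with 2.5% each would cost more: power for the binary test falls to 71.5% at 62 per arm, and restoring 80% needs 75 per arm, or 150 / 0.86 = 174.4, rounded up to 175 patients.
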